### Primary end points

The primary end point is the 3-year graft failure rate in HLA Ab + patients. Graft failure will be defined as restarting long-term dialysis or requiring a new transplant. Time zero starts at the time of randomisation, once the result of the HLA test is known. For those patients who are HLA Ab– at randomisation but become Ab + during a subsequent screening, time zero will be reset at the time of the positive test, and the follow-up time will be extended to allow for the 3-year end point.

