We hypothesise that the experimental treatment will bring the failure rate of group B2 down to that of biomarker negative patients in standard care (C). Assuming a 16% failure rate for group A2 (as in
[8]), and a 6% failure rate for group B2, 146 patients per group will provide 80% power and 5% type I errors, for a two-sided test.

The numbers enrolled in groups A and B include those patients initially enrolled in groups C or D who become HLA Ab + during re-screening.

We calculated the sample size needed to show the non-inferiority of all unblinded patients compared to all blinded patients as follows.

Hypothesis 2: All patients randomised to unblinded screening (combined groups B1 + B2 + D) will show equal or lower graft failure rates than all patients randomised to blinded screening (combined groups A1 + A2 + C), irrespective of biomarker status.

At the end of the trial, we expect 60% of patients to be in the HLA Ab– groups, 13% in DSA + groups and 27% in non-DSA + groups (after dropouts). Assuming a 6% failure rate in biomarker negative groups C and D, the estimated average failure rate of all blinded screening patients is 11.8% (that is, (6 × 0.6) + (16 × 0.27) + (30 × 0.13)). Similarly, the estimated average failure rate in the unblinded screening group is 7.3%. We have established a non-inferiority limit of 5% absolute difference, so that the unblinded group would be considered non-inferior with a failure rate of 16.8% or lower. For this purpose, 1,043 patients in each arm would provide 90% power and 2.5% (one-sided) type I errors.

We will keep recruiting until every group has acquired the number required to test both hypotheses. When calculating the number of patients to screen for eligibility and to recruit, the following assumptions were made: (1) 60% of patients under follow-up at each transplant centre will meet the eligibility criteria, (2) 10% will refuse consent, (3) the prevalence of HLA Ab in most transplant populations is 25% to 30%, (4) 6% of initially Ab– patients will become Ab + in each screening round and (5) 2% will drop out every screening round.

Based on these assumptions and a recruitment audit in participating centres, we have estimated that we need to assess eligibility for 4,672 patients and enrol 2,522 to ensure sufficient numbers are in each group at the primary end point to test both hypotheses. Figure 

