### Statistical analysis

#### Primary analysis

Statistical analysis will be on an intention-to-treat and treatment-received basis. We will consider the patients who become positive during the follow-up in the appropriate group.

The proportion of graft failures for each of the groups is denoted by π_A1_, π_B1_, etc.

Superiority (hypothesis 1):

H_0_: π_A1_ = π_B1_ and π_A2_ = π_B2_

H_1_: π_A1_ ≠ π_B1_ and π_A2_ ≠ π_B2_

To test superiority for the primary outcome for the biomarker (HLA Ab) positive groups (hypotheses 1.1 and 1.2), we will use a two-sided *Z*-test at the 5% level of significance, and will calculate the 95% CI for the difference in the proportion of graft failures between the biomarker-led care and standard care groups. The biomarker-led care groups will be considered superior if the absolute *Z* > 1.96, and our assumptions with respect to the size of the differences will supported if the CI includes a positive difference in proportions of 14% for hypothesis 1.1, and 10% for hypothesis 1.2.

Non-inferiority (hypothesis 2):

H_0_: π_Unblind_ – π_Blind_ ≥ δ

H_1_: π_Unblind_ – π_Blind_ < δ

To test for non-inferiority of the unblinded groups compared to the blinded groups (hypothesis 2), we will carry out a one-sided *Z*-test at the 2.5% level of significance. We will conclude non-inferiority if H_0_ is rejected, and the corresponding upper bound of the 95% CI excludes the limit δ (set at 5% more failures in the unblinded groups).

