#### Secondary analysis

A similar procedure will be followed for secondary binary outcomes. We will use Cox proportional hazards regression to analyse survival outcomes. For continuous secondary outcomes we will use a two-sample *t*-test, transforming data where they are skewed.

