### Handling missing data

Where a given outcome is measured at two or more time points, missing post-randomisation assessments will be dealt with by fitting linear mixed models to all the available measures using maximum likelihood methods. Such an approach provides valid inferences under the assumption that the missing data mechanism is ignorable (or Missing at Random). If post-randomisation variables are found to be predictive of the dropout rate, multiple imputation will be considered using *K*-nearest neighbours.

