### Procedures for assessing efficacy parameters

Graft failure is defined as the return to long-term dialysis or re-transplantation. This will be measured from the date of recruitment and will be reported for failure due to any cause. The date of restarting dialysis or re-transplantation will be recorded on the Case Report Form.

Deteriorating renal function will be determined by linear regression analysis of the serial MDRD eGFRs from the point of recruitment (like that used by Dudley *et al*.
[14]). Deterioration is defined as a negative slope. To be valid, the linear regression should yield an adjusted *r*^2^ ≥ 0.35 and have *P* ≤ 0.05 for the slope value. Stable renal function will be defined as serial MDRD eGFRs that are not significantly different from the horizontal baseline (that is, *P* > 0.05 on linear regression analysis). An improvement in renal function will be defined as a change in the slope so that it becomes positive. Serum creatinine levels and MDRD eGFR for the 12 months preceding recruitment and for the whole time patients are on the trial will be recorded on the CRF.

Proteinuria is defined by the PCR of a urine sample and is significant if >50. The PCR will be recorded on the CRF.

Acute rejection is defined by a combination of: (a) an acute rise in serum creatinine prompting a renal biopsy and (b) any pathology on the biopsy that meets the criteria for acute rejection, according to the latest BANFF criteria. The number of biopsies and the appropriate biopsy reports will be recorded on the CRF.

A full economic evaluation will adopt a National Health Service (NHS) perspective. The 3-year outcomes are the rates of: (1) graft failure, (2) patient survival, (3) graft dysfunction (see definition above), (4) acute rejection and (5) culture-positive infection, malignancy or diabetes, together with (6) EQ-5D, which is a patient-specific quality-adjusted life years (QALY) measurement. Cost-effectiveness will use (1) to (5) where (1) is the primary and the others are secondary outcomes. Cost-utility will be measured using (6) (the EQ-5D questionnaire). The net benefit per patient will be calculated by multiplying QALY by the assumed maximum willingness-to-pay for QALY (£20,000 per QALY) and subtracting the costs. The costs of all interventions will be obtained from Guy’s or estimated by identifying relevant categories of resource utilisation or measuring the volume of each category and multiplying by the average NHS resource costs

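### The primary test uses crude 3-year proportions although dropout is expected, and the committed missing-data method does not fit a once-only event; a 36-month cumulative-incidence difference would use the follow-up of those lost

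*Protocol article*

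**What the plan says.** All places are in the protocol article.

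- *Primary end points*: "The primary end point is the 3-year graft failure rate in HLA Ab + patients". The event is narrow: "Graft failure will be defined as restarting long-term dialysis or requiring a new transplant". Patient survival is listed separately under *Secondary end points*.
- *Primary analysis*: analysis is by intention to treat and by treatment received. Superiority is judged by a two-sided Z-test at 5%, and the authors "will calculate the 95% CI for the difference in the proportion of graft failures between the biomarker-led care and standard care groups". Non-inferiority of unblinded to blinded screening is a one-sided Z-test at 2.5% against a 5-point margin.
- *Sample size calculations*: one planning assumption is that "2% will drop out every screening round". Rounds are 8 months apart.
- *Handling missing data*: for outcomes measured at two or more time points, "missing post-randomisation assessments will be dealt with by fitting linear mixed models to all the available measures". If post-randomisation variables turn out to predict dropout, K-nearest-neighbour multiple imputation is to be considered.
- *Secondary analysis*: "We will use Cox proportional hazards regression to analyse survival outcomes". No time-to-event method is named for the primary outcome.
- *Procedures for assessing efficacy parameters*: of graft failure, "This will be measured from the date of recruitment and will be reported for failure due to any cause"; and "The date of restarting dialysis or re-transplantation will be recorded on the Case Report Form".

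**The concern.** A 3-year proportion is unambiguous only if everyone is followed for three years or has failed before then. The plan expects some patients to be lost and does not say what becomes of them in the numerator or denominator. Its missing-data section does not close the gap, because its committed method is for repeated continuous measures. The adjusted models under *Exploratory moderator analysis*, which may be taken as final, use the same binary outcome and inherit the problem.

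At stake is bias more than power. The trial is open-label and only one side changes treatment, so loss to follow-up could differ between arms. If dropouts are counted as non-failures, the arm that loses more patients looks better. In the non-inferiority test that rule pulls both failure rates down and shortens any true excess in the unblinded arm, which favours the conclusion sought. The recorded failure dates would avoid the choice, but the primary test does not use them.

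**Working it through.** **Inputs.** Planned 3-year failure rates: 30% v 16% (hypothesis 1.1), 16% v 6% (hypothesis 1.2), 11.8% blinded with a limit of 16.8% unblinded (hypothesis 2). Dropout is 2% per 8-month round. A constant rate of graft loss is the plan's own expectation for standard care (*Discussion*); I apply it to every group.

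**Plan's sample sizes.** With n = 2(1.96 + 0.84)²/h² and h = 2·asin√p1 − 2·asin√p2, the results are 138.8 and 145.8, that is 139 and 146 per group as stated. So the stated sizes match a comparison of simple proportions.

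**Dropout.** 36/8 = 4.5 rounds, so 1 − 0.98^4.5 = 8.7%. A patient followed for the full six years has nine rounds: 1 − 0.98^9 = 16.6%, counted from randomisation. For superiority a converter's clock restarts at the positive test, so I use 8.7% below.

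**Effect of the unstated rule.** Write f = −ln(1 − p) and g = −ln(1 − d), with d = 0.087 and g = 0.0909. Failures seen before dropout = [f/(f + g)]·[1 − (1 − p)(1 − d)]; dropouts before failure = the same with g on top. For p = 0.30: f = 0.3567, 1 − 0.70 × 0.913 = 0.3608, so 0.797 × 0.3608 = 28.75% seen to fail and 7.33% lost. Excluding the lost: 28.75/(100 − 7.33) = 31.0%.

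| True rate | Seen to fail (lost = non-failure) | Lost | Lost excluded |
|---|---|---|---|
| 30% | 28.75% | 7.33% | 31.0% |
| 16% | 15.31% | 7.99% | 16.6% |
| 6% | 5.74% | 8.43% | 6.3% |

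Differences (from unrounded rates):

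| | Lost = non-failure | Lost excluded | Time-to-event, non-informative dropout |
|---|---|---|---|
| Hypothesis 1.1 | 13.4 | 14.4 | 14.0 |
| Hypothesis 1.2 | 9.6 | 10.4 | 10.0 |

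**Extreme imputation.** Hypothesis 1.1: from 28.75 − (15.31 + 7.99) = 5.45 to (28.75 + 7.33) − 15.31 = 20.8 points. Hypothesis 1.2: from 15.31 − (5.74 + 8.43) = 1.1 to (15.31 + 7.99) − 5.74 = 17.6 points. These are bounds, not expectations.

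**Unequal dropout (assumed 5% v 15%), no true effect.** At a 30% failure rate, counting the lost as non-failures gives 29.3% v 27.8%, a false 1.5 points in favour of the arm with more dropout; at 16% it is 0.8 points. Excluding the lost gives 30.6% v 31.9% at the 30% rate, an error of 1.3 points the other way.

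**Non-inferiority.** Treat each arm's average rate as one group and let the truth lie at the limit. With 8.7% dropout in both arms and the lost counted as non-failures, 16.8% appears as 16.1% and 11.8% as 11.3%, so a true 5.0-point excess appears as 4.8. With 15% dropout in the unblinded and 5% in the blinded arm (assumed) it appears as 15.5 − 11.5 = 4.0 points; with the reverse, as 16.4 − 10.9 = 5.5.

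**Power.** If 139 and 146 were numbers entered, a 36-month time-to-event estimate (Greenwood variance) has about 78% and 77% power, against 80% and 79% without dropout on the same scale. Having 139 and 146 remain at month 36 needs 139/0.913 → 153 and 146/0.913 → 160 entered. Enrolment of 2,522 is already sized for numbers at the end point.

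**Why death needs a competing-risk estimate.** The article gives no death rate. For an assumed 3-year death risk of 5% to 10%, the first formula with d replaced by the death risk gives a cumulative incidence of failure in the 30% group of 29.3% to 28.6%. A Kaplan–Meier estimate that censors deaths would still show 30%, an overstatement of 0.7 to 1.4 points.

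**The case against.** The strongest reply has four parts.

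1. *A fixed-horizon proportion is legitimate and the harm is small.* With equal dropout the differences move by only 0.4 to 0.6 points, and enrolment protects power. That stands; the larger errors need unequal or informative dropout.
2. *Handling of lost patients belongs in the analysis plan, and a journal article condenses.* This would be decisive if the article were silent. It is not: it fixes the primary test, and it contains a missing-data section whose committed method cannot serve that test.
3. *The missing-data section confines mixed models to outcomes measured more than once and has an imputation fallback.* True, and imputation could serve a binary outcome. But it is triggered only if predictors of dropout are found, and even then is only to be considered.
4. *Under Withdrawal of subjects, intolerance is no reason to withdraw, and follow-up is sought after stopping drug.* This should reduce loss, but the plan still budgets for it.

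A reader might go further in three ways that the article does not support. First, that 2,522 − 2 × 1,043 = 436 enrolled patients go unanalysed: 1,043 per arm is a power requirement, the analysis is declared intention-to-treat, and the recruitment target carries a margin of error. Second, that deaths with a working graft have no valid place: by the stated definition they are non-failures, and with complete follow-up the crude proportion is a proper cumulative incidence. Third, that excess mortality from the intervention would slip under the margin by a known amount: no death rate is given from which to size it.

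**Conclusion.** The concern holds in a limited form. The primary test, the expected dropout and the committed missing-data method do not fit together, and the result depends on a rule that the article does not give. The size is modest under equal dropout: 0.4 to 0.6 points on planned differences of 14 and 10, and 0.2 points off a true 5-point excess. It reaches about 1 to 1.5 points if dropout is 5% in one arm and 15% in the other, which is an assumption. These figures rest on constant failure and dropout rates and on dropout that is unrelated to prognosis.

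On death the finding is only that its status is implicit. The competing-risk estimate does not count deaths as failures either. Its merit is that it keeps the stated end point while handling dropout properly; mortality is made visible by the supportive composite and the existing survival end point.

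**What to change.** - Make the primary estimate the difference in 36-month cumulative incidence of graft failure, in all randomised patients belonging to each comparison, counted from the stated time zero. Censor dropouts at last contact and treat death with a functioning graft as a competing event (Aalen–Johansen estimate).
- Use its standard error for the Z statistic and the 95% CI. It stays on the absolute scale, so the 14%, 10% and 5% figures apply unchanged.
- State outright that death with a working graft is not a graft failure. Report graft failure or death combined as a supportive sensitivity analysis for both hypotheses, not as a condition for success.
- Restrict the linear mixed models to eGFR and other repeated measures.

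The cost is wording. Failure dates are already on the Case Report Form; dates of death and last contact should follow from the survival end point and the 4-monthly visits, but this should be confirmed. The price is the assumption of non-informative dropout.

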### Sample size calculations

The primary purpose of this trial is to demonstrate superior outcomes using a defined treatment strategy compared to standard care for biomarker (HLA Ab) positive patients. Once superiority is demonstrated for HLA Ab + patients, it is also necessary to demonstrate non-inferior outcomes when comparing the unblinded screening strategy to the blinded standard of care for the entire patient population, including those HLA Ab–. The graft failure rate 3 years after screening has been chosen as a clinically relevant primary outcome. As a reference for power calculations, we have used the observed failure rates reported by Lachmann *et al*.
[8] for HLA Ab + and HLA Ab– patients. Since failure rates differ between DSA + and non-DSA + patients, sample size calculations have been carried out separately for these groups. Following these calculations, we estimated the number to be screened, based on expected dropout rates, expected screening results and eligibility criteria (see below). We based our estimates of the differences in primary outcome between the groups on, first, the results of our preliminary data from patients with CR treated with a similar regime as used here, and second, our assessment that large differences in primary outcome will be needed to make the screening programme cost-effective.

Hypothesis testing will be sequential
[11]. Superiority will be tested first in the HLA Ab + groups to demonstrate the efficacy of the treatment. If this analysis is significant, then non-inferiority will be tested for the entire population to demonstrate the clinical utility of the biomarker screening. We calculated the sample size needed to show the superiority of the treatment optimisation for biomarker-positive patients using the hypotheses as follows.

Hypothesis 1.1: HLA Ab + patients with DSA, randomised to standard care (A1) will show higher graft failure rates than patients randomised to biomarker-led care (B1).

We hypothesise that the experimental treatment will bring the failure rate of group B1 down to that of non-DSA patients in standard care (A2). Assuming a 30% failure rate for group A1 (as in
[8]), and a 16% failure rate for group B1, 139 patients per group will provide 80% power and 5% type I errors, for a two-sided test.

Hypothesis 1.2: HLA Ab + patients, with non-DSA, randomised to standard care (A2) will show higher graft failure rate than patients randomised to biomarker-led care (B2).

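### The superiority rule and the gate to hypothesis 2 carry no direction, at odds with hypotheses 1.1 and 1.2, and a separate statement treats a confidence interval that merely contains the planned effect as support for it

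*Protocol article*

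**What the plan says.** The Sample size calculations section states hypothesis 1.1 with a direction: "HLA Ab + patients with DSA, randomised to standard care (A1) will show higher graft failure rates than patients randomised to biomarker-led care (B1"). Hypothesis 1.2 does the same for the non-DSA groups, A2 and B2. That section describes the gate to hypothesis 2 in two ways: "Once superiority is demonstrated for HLA Ab + patients" and, as the sequential rule, "If this analysis is significant, then non-inferiority will be tested for the entire population".

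The Primary analysis section then gives the operative rules for hypothesis 1:
- the test: "we will use a two-sided *Z*-test at the 5% level of significance";
- the alternative, which is undirected: "H_1_: π_A1_ ≠ π_B1_ and π_A2_ ≠ π_B2";
- the decision: "The biomarker-led care groups will be considered superior if the absolute" Z exceeds 1.96;
- a further statement that the assumed sizes of the differences will be supported "if the CI includes a positive difference in proportions of 14% for hypothesis 1.1, and 10% for hypothesis 1.2".

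It does not say which arm is subtracted from which in hypothesis 1. For hypothesis 2 it does: unblinded minus blinded, so that a positive value means more failures under unblinded screening.

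**The concern.** A two-sided test is sound. The fault is that both tails carry the label of superiority. The Primary analysis section is the only place that defines when superiority is declared, and its definition does not match the directional hypotheses. The gate inherits the gap, because a significant result opens it whatever its sign.

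The second statement is a different and lesser fault. A confidence interval that contains 14 points shows only that 14 points is not excluded. The same interval may contain 0, a wider interval contains more values, and a benefit clearly larger than planned can leave 14 points outside. Because the sign is undefined, a reader who applied hypothesis 2's convention to hypothesis 1 would take a positive difference as harm.

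At stake are the prespecified decision on the primary end point, entry to hypothesis 2, and how the result is described against the planning assumptions. The Secondary analysis section applies a similar procedure to secondary binary outcomes, so the wording carries over.

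**Working it through.** **Inputs from the protocol article (Sample size calculations).** Hypothesis 1.1: 30% v 16%, 139 per group. Hypothesis 1.2: 16% v 6%, 146 per group. Both use a two-sided 5% level and 80% power. Hypothesis 2: 1,043 per arm, 5-point margin, mix of 60% antibody-negative, 27% non-DSA and 13% DSA.

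**Reproducing the plan's sample sizes.** With h = 2·arcsin√p1 − 2·arcsin√p2 and n = 2(1.960 + 0.842)²/h²:
- 30% v 16%: h = 0.3362, n = 138.8, so 139.
- 16% v 6%: h = 0.3281, n = 145.8, so 146.

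Both stated figures are reproduced.

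**Superiority rule.** Let d = standard care minus biomarker-led care, and Z = d/√(2p(1−p)/n) with p the pooled proportion. Examples of harm that meet the literal rule:
- n = 139, failures 42 (standard) v 58 (biomarker-led): d = 30.2% − 41.7% = −11.5 points, p = 0.3597, standard error 0.0576, Z = −2.00.
- n = 146, failures 23 v 37: d = 15.8% − 25.3% = −9.6 points before rounding, p = 0.2055, standard error 0.0473, Z = −2.03.

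How often the literal rule is met, by full binomial enumeration (the harm rates are illustrative assumptions):

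| True rates, standard v biomarker-led | n per group | abs(Z) > 1.96 | Z > +1.96 only |
|---|---|---|---|
| 30% v 30% | 139 | 5.0% | 2.5% |
| 30% v 37% | 139 | 23.6% | 0.1% |
| 30% v 44% | 139 | 68.5% | below 0.1% |
| 16% v 26% | 146 | 55.7% | below 0.1% |
| 30% v 16% (as planned) | 139 | 79.9% | 79.9% |

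The last row shows that a direction condition costs no power.

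**What follows if the gate opens.** Blinded rate: 0.60×6 + 0.27×16 + 0.13×30 = 11.8%.
- Harm in DSA only (41.7%), other groups equal: unblinded rate 3.6 + 4.32 + 5.42 = 13.3%. Difference 1.5 points, 95% CI −1.3 to 4.4, inside the margin. The chance of concluding non-inferiority is about 67%.
- Harm in both strata (41.7% and 25.3%): difference 4.1 points before rounding, CI 1.1 to 7.0. Non-inferiority fails at that result.

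**Inclusion statement.** Wald interval d ± 1.96√(pA(1−pA)/n + pB(1−pB)/n):
- n = 139, failures 42 v 37: d = 3.6 points, CI −7.0 to 14.2, Z = 0.66. Counts as support for 14 points.
- n = 146, failures 23 v 20: d = 2.1 points, CI −6.1 to 10.2, Z = 0.50. Counts as support for 10 points.
- n = 139, failures 42 v 10: d = 23.0 points, CI 14.3 to 31.8. Does not count.

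How often it is met (all true rates here are assumptions):

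| True rates | n per group | CI includes target |
|---|---|---|
| 16% v 16% (target 14) | 139 | 10.8% |
| 23% v 23% (target 14) | 139 | 20.5% |
| 30% v 30% (target 14) | 139 | 27.6% |
| 30% v 30% (target 14) | 50 | 65.6% |
| 16% v 16% (target 10) | 146 | 35.7% |
| 16% v 16% (target 10) | 50 | 71.0% |
| 30% v 23% (target 14) | 139 | 73.5%; 46.8% include 0 as well |
| 35% v 10% (target 14) | 139 | 36.7% |

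The 50-per-group rows only show the effect of lower precision; the plan intends the full numbers.

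**The case against.** The strongest reply is that direction is fixed elsewhere. Hypotheses 1.1 and 1.2 say which arm should fail more often, the stated purpose is to show superior outcomes, one wording of the gate requires superiority, and an absolute Z above 1.96 is common shorthand for a two-sided 5% test. This stands as to intent. A reader might infer that the trial is set to announce harm as success; the documents do not support that. What remains is that the operative rule says less than the hypotheses it is meant to test.

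A reader might also infer that significant harm would carry the trial through hypothesis 2. Opening that test does not pass it, as the case of harm in both strata shows. The alternative for hypothesis 1 also joins the two strata with an and. If the gate follows that wording, harm in DSA patients with no difference in non-DSA patients would not open it.

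Finally, the inclusion statement might be read as part of the primary decision. It is not: superiority rests on Z and the gate on significance. A 35% v 10% benefit would be declared superior in 99.9% of trials whether or not the interval contains 14 points. The full group sizes are also intended, since recruitment is to continue until every group has its number. The statement is therefore a loose check of planning assumptions, but the inference it draws is still wrong at the planned sizes.

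**Conclusion.** Both points hold and should be fixed; neither calls for a redesign. The undirected rule and gate conflict with the directional hypotheses. Taken literally, they admit a wrong-direction result in 2.5% of trials per comparison under no effect, and in about 69% under an assumed 44% v 30% at 139 per group. The inclusion statement decides nothing but is invalid. With no true effect it is met in about 11% to 28% of trials for hypothesis 1.1 (assumed common rate 16% to 30%) and about 36% for hypothesis 1.2 (16% in both arms). It is met more often as precision falls, and a true 35% v 10% benefit meets it in only 37%. These figures assume independent binomial outcomes, the planned group sizes, the pooled Z-test and the Wald interval. The analysis plan is not at hand, but these are rules the article states, not details it leaves open.

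**What to change.** Keep the two-sided 5% test and change the wording of the Primary analysis section:
- Define the difference for hypothesis 1 as standard care minus biomarker-led care.
- Declare superiority only if its 95% confidence interval lies wholly above 0, that is Z > +1.96 in favour of biomarker-led care.
- Let only that result open hypothesis 2, and use the same wording for the gate in Sample size calculations.
- Report Z < −1.96 as evidence of harm.
- Replace the sentence about intervals that include 14% or 10% with reporting of the estimate and its 95% confidence interval.

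The cost is a few sentences. The sample size is unchanged, because a one-sided 2.5% criterion uses the same critical value as the two-sided 5% test.
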